### Recruitment, consent, and allocation to interventions

Participants will be recruited by local advertisements and recruitment talks in the San Francisco Bay Area, online dementia caregiving groups, and by accessing an established research registry database. Recruitment is planned to continue until 40 eligible participants are enrolled (20 per intervention arm), and the approximate recruitment period is 2 months. Participants will not receive financial compensation for taking part in the study, and there will be no inducements for completing interventions. Participants deemed suitable for recruitment, will be contacted *via* email or phone with an opportunity to participate in additional eligibility screening, and to complete an online screening questionnaire to confirm eligibility. A follow-up email will include a review of study details (e.g., start date, expectations).

All screening and recruitment conversations will be completed by research personnel trained in the ethical conduct of human subjects’ research. Informed written consent will be obtained *via* interview with a trained examiner (*via* Zoom), during which the study will be clearly explained in detail, and caregivers will be able to ask questions prior to enrollment. Caregivers will also be informed that they can drop out of the study at any time. After this conversation, those agreeing to participate will be asked to formally consent to study participation. Due to current pandemic restrictions, DocuSign will be used to obtain participants’ consent signatures electronically. The amount of time expected for this consenting process is 20 min.

Next, for the baseline assessment part of the study (T0, 0 months), enrolled participants will be scheduled to participate in a 10-min semi-structured online interview *via* Zoom (see Supplementary material) and will complete a set of online surveys and performance tasks *via* Qualtrics. Those evaluations are designed to minimize possible subject fatigue, stress, and boredom. Breaks from testing will be allowed, and testing sessions may also be broken into multiple sessions. After all participants have completed enrollment and baseline assessment, they will be randomized to one of the two study arms and will then be informed *via* email of the group to which they have been assigned (see Figure 1; Table 1).

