#### Primary outcome: Relational well-being

We hypothesize that participants in the MBSR intervention will experience positive changes in their interpersonal relationships and their ability to perceive and correctly interpret social signals from pre- to post-intervention, and that these changes will be more pronounced than those seen in the active control group. We included a number of measures of caregivers’ relational well-being.

To measure caregivers’ experiential avoidance, the Experiential Avoidance Caregiver Questionnaire (EACQ) will be used (Losada et al., 2014). Participants will rate their tendency to avoid unwanted caregiving experiences on a 5-point Likert scale from 1 (not at all) to 5 (a lot). The EACQ has been shown to have good internal consistency (Cronbach’s alpha; 0.60–0.71). The validity indexes suggest that EACQ is associated with other scales or constructs (e.g., anxiety, depression or alexithymia) in the expected directions. The EACQ may prove to be a useful tool for the identification of avoidance which can be frequently observed in distressed dementia caregivers, and which may explain the maintenance or exacerbation of their high levels of anxiety or stress.

To examine subjective sense of caregiver burden, the Zarit Burden Interview short form (ZBI-12), will be used (Higginson et al., 2010). Participants will rate their perceived burden on a 5-point Likert scale from 0 (*never*) to 4 (*nearly always*). The ZBI-12 has been shown to have good internal consistency (Cronbach’s alpha; 0.69–0.89). No loss of reliability or validity appear to result from reduction of items from the original scale. Consistent with the findings previously reported this measure appears to be an effective measure of caregiver burden (Bédard et al., 2001).

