### Data analysis plan

The study will use mixed methods, integrating quantitative and qualitative strategies, making no assumptions about linear relationships between quantitative and qualitative data/findings (DePoy and Gitlin, 1994). These two strategies will be employed as different ways of exploring and understanding the theme in question, i.e., mindfulness and caregiver wellbeing.

Regarding quantitative measures we will first identify factors that are confounders between the two intervention groups, which may include socio-demographics, relationship to care recipients, healthcare access, socioemotional support, dementia patient diagnosis, engagement in intervention, relationship quality with facilitator, hours (weekly) spent with the person with dementia. Any variables showing significant group differences will then be considered confounds and included in the main statistical analyses. We will also check for missing data and signs of systematic response bias in self-reported responses. The main analysis will evaluate the effect of treatment group x time (t0, t1, t2). All participant outcome measures (domains: relational well-being, psychological well-being, dementia patient’s lifestyle changes), will be analyzed using generalized linear mixed models. Models will treat treatment and time points (including their interaction) as fixed effects and caregivers as random effects. We will look for a main treatment effect, a main time effect, and an interaction effect of treatment by time. All hypotheses will be individually evaluated at a nominal *p*-value of 0.05.

Semi-structured interviews will be analyzed using thematic analysis. First, grounded theory’s open coding stage will be employed, followed by axial coding and analyses (Spradley, 1979; Charmaz, 2006). We will identify meaningful themes and conceptualize our findings in relation to existing mindfulness theories and stress reactivity research. Because the first two authors are mindfulness teachers who have worked extensively with older adults, including dementia caregivers, qualitative data will be analyzed separately and jointly by the first two authors. Final synthesis of analyzed data will be obtained through continuous discussions among the research team until consensus is reached.

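### The treatment-by-time model is valid but gives up precision by treating the pre-randomisation score as a free outcome level, and the treatment and time main effects tested beside it do not measure benefit

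*Protocol article*

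**What the plan says.** All points are in the protocol article.

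- **Main analysis** (Data analysis plan): "The main analysis will evaluate the effect of treatment group x time (t0, t1, t2"), so t0 is one of three modelled outcome times.
- **Model** (same section): "Models will treat treatment and time points (including their interaction) as fixed effects and caregivers as random effects".
- **Effects examined** (same section): "We will look for a main treatment effect, a main time effect, and an interaction effect of treatment by time". On the threshold: "All hypotheses will be individually evaluated at a nominal *p*-value of 0.05".
- **Covariates** (same section): "Any variables showing significant group differences will then be considered confounds and included in the main statistical analyses". The candidates listed do not include the baseline score of the outcome being analysed.
- **Hypothesis** (Primary outcome: Relational well-being): changes in the mindfulness arm "from pre- to post-intervention, and that these changes will be more pronounced than those seen in the active control group".
- **Timing of t0** (Recruitment, consent, and allocation to interventions): "After all participants have completed enrollment and baseline assessment, they will be randomized to one of the two study arms".

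**The concern.** The hypothesis is a between-arm difference in pre-to-post change. Of the three effects the plan will examine, only the interaction addresses it.

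- **Treatment main effect.** The t0 score precedes allocation, so the true arm difference at t0 is zero. Averaging over t0, T1 and T2 mixes that zero into the estimate.
- **Time main effect.** It pools both arms. The control arm is an active programme, so both arms may improve and the effect may be significant when mindfulness adds nothing.
- **Baseline as a free outcome level.** Separate arm means at t0 make the interaction work like a change score. It removes each caregiver's own level, but less efficiently than conditioning on the baseline score.

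Precision matters here because the trial is small: 20 per arm before attrition. The Sample size calculation section says the study is to establish preliminary effect sizes. A main effect that is two thirds of the sustained effect would be a misleading figure to carry into a later trial.

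**Working it through.** **Inputs from the article.** 20 per arm, 1:1 (Recruitment section); 80% retained through T1 (Strategies for improving adherence), so n = 0.8 × 20 = 16 per arm; nominal 0.05, taken as two-sided; three assessments.

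**Assumptions.** The article gives no within-person correlation ρ, no trajectory of effect and no retention figure for T2. I take ρ = 0.5, 0.6 and 0.7, outcome SD 1, equal correlation between all visits, 16 per arm at both follow-ups, and 0.70 SD as an illustrative effect.

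**The article's own power figure.** It states 80% power for r ≥ 0.70 and 25% for r ≥ 0.50. At 16 per arm, reading r as a standardised mean difference gives 48% and 28%. Reading it as a correlation in 32 people gives 99.7% and 84%. Neither reproduces the stated pair. That is a separate matter, and nothing below depends on it.

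**1. Precision lost by not adjusting for baseline**

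Per-arm variance is 2(1−ρ) for the T0-T1 change contrast and 1−ρ² for the baseline-adjusted T1 contrast. The ratio is 2/(1+ρ):

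- ρ = 0.5: 1.00/0.75 = 1.33
- ρ = 0.6: 0.80/0.64 = 1.25
- ρ = 0.7: 0.60/0.51 = 1.18

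**2. Dilution of the treatment main effect**

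- Sustained effect: (0 + 0.70 + 0.70)/3 = 0.47 SD, two thirds of 0.70.
- Effect halved by T2: (0 + 0.70 + 0.35)/3 = 0.35 SD, one half.

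**3. Power, effect sustained at 0.70 SD**

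- Main effect: noncentral t, 30 df, noncentrality 0.467/√[((1+2ρ)/3)(2/16)] = 1.62, 1.54, 1.48.
- T0-T1 change: 30 df, 0.70/√[2(1−ρ)(2/16)] = 1.98, 2.21, 2.56.
- Baseline-adjusted T1: 29 df, 0.70/√[(1−ρ²)(2/16)] = 2.29, 2.47, 2.77.
- Interaction: noncentral F on 2 and 60 df, λ = 16·Σ(δ−mean δ)²/[2(1−ρ)]. Here Σ = 0.467² + 2 × 0.233² = 0.327, so λ = 5.23, 6.53, 8.71.
- Baseline-adjusted joint T1/T2 test: F on 2 and 28 df, λ = (16/2)·δ′S⁻¹δ, where S has diagonal 1−ρ² and off-diagonal ρ−ρ². This gives λ = 7.84, 8.91, 10.89.

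| ρ | Main effect | Interaction | T0-T1 change | Adjusted T1 | Adjusted joint T1/T2 |
|---|---|---|---|---|---|
| 0.5 | 35% | 50% | 48% | 60% | 66% |
| 0.6 | 32% | 60% | 57% | 67% | 72% |
| 0.7 | 30% | 73% | 70% | 76% | 81% |

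Simulation (20,000 runs per setting, ρ = 0.5 and 0.7) agreed to about 2 points for the main effect, the interaction and adjusted T1. With no true effect and ρ = 0.7, the interaction rejected in 4.9% of runs.

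**4. Dependence on trajectory, ρ = 0.6**

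| Effect at T1, T2 (SD) | Interaction | Adjusted T1 | Adjusted joint T1/T2 |
|---|---|---|---|
| 0.70, 0.70 | 60% | 67% | 72% |
| 0.70, 0.35 | 47% | 67% | 55% |
| 0.35, 0.70 | 47% | 22% | 55% |

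Whether adjusted T1 beats the interaction depends on when the benefit appears. The adjusted joint test beats the interaction in all three rows.

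**The case against.** The strongest reply is that the plan's three effects do not have equal rank. Treatment by time is named as the main analysis, it is the between-arm difference in change, and that is what the hypothesis predicts. It holds its type I error and already uses baseline implicitly. This stands. A reader might infer that the main analysis is biased or misses the hypothesis; the article does not support that. Nor does it say that a treatment or time main effect would by itself count as benefit. The risk is that both are listed for testing at 0.05 with no statement of how they will be read.

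A second reply is that follow-up contrasts and coding are details a condensed article may leave to the full plan. This stands in part. The 2-df form of the interaction test is inferred from the three listed times and the absence of a named contrast, and not naming one is no fault in itself. But the article does state the effects to be examined and the place of t0 in the model, and the point rests on those.

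A third reply is that a T1 contrast is not always more powerful. This also stands. A reader might infer that the interaction is uniformly the weaker test, but if the effect is 0.35 SD at T1 and 0.70 SD at T2 the order reverses, 47% against 22%. At ρ = 0.8 with a sustained effect the two tie at about 89%.

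The exploratory aim lowers the stakes of any single test. It does not help the main effects, because an effect-size estimate diluted by t0 is a poor product of a pilot.

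**Conclusion.** The point holds as a loss of precision plus two effects that should not be read as efficacy; the main analysis itself is valid and on target.

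- **Precision.** The unadjusted T0-T1 contrast has 18% to 33% more variance than the adjusted one for ρ from 0.7 down to 0.5.
- **Treatment main effect.** It estimates two thirds of a sustained effect whatever the correlation, and one half if the effect halves by T2. Its power of 30-35%, against 60-76% for adjusted T1, assumes a sustained 0.70 SD and 16 per arm.
- **Time main effect.** It carries no between-arm information.

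Correlation, effect size, trajectory and T2 retention are assumptions. The zero true difference at t0 holds for everyone randomised. Strategies for improving adherence restricts the analysis to participants who meet arm-specific participation thresholds, and in that subset equality at t0 is no longer guaranteed by randomisation.

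**What to change.** 1. Fit the same mixed model with a common t0 mean for both arms, or model T1 and T2 as outcomes with the t0 score of that measure as a prespecified covariate, whether or not the arms differ significantly at baseline. The common-mean version is justified for all randomised participants; if the analysed set stays restricted, use the covariate version and say so.
2. For each measure, report the mindfulness-minus-control difference at T1, which matches the pre-to-post hypothesis, and at T2, with confidence intervals.
3. State that neither the treatment main effect averaged over t0 nor the time main effect counts as evidence of benefit.

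The cost is analysis-plan wording; data and software are unchanged. The downside is that naming T1 as lead contrast loses power against the interaction if the benefit emerges mainly by T2 (22% against 47% in the example above). Where that is a concern, lead with the baseline-adjusted joint T1/T2 test, which reaches 55% in the same case, and report the two time-specific differences beside it.

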## Abstract

Dementia caregiving, besides encompassing various challenges in tandem to the diagnosis of the care recipient, is associated with decreased psychological well-being and mental health. Accordingly, caregivers’ wellbeing has an impact on the quality of care they provide and on the relationship quality with the person in their care. The aim of the present study is to examine the effectiveness of a mindfulness-based intervention on relational and psychological wellbeing, tailored to the needs of dementia caregivers. This clinical trial (NCT04977245) will apply a randomized controlled mixed method design. Caregivers will be randomly allocated to either the mindfulness intervention or the active control group. The intervention arm is based on experiential learning and is targeted to promote caregivers’ well-being and empowerment. Assessments will include, standardized self-report questionnaires, task performance measures, and qualitative measures. All assessments will be held at three time points (baseline; t0, 0 months, post-intervention; t1, 2 months, and after maintenance; t2, 3 months) focused on three core domains (1. relational well-being, 2. psychological well-being, and 3. dementia patient’s lifestyle/activities). The primary outcome will be relational well-being, and data will be analyzed using linear mixed modelling.

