### Outcome measures

Assessment methods (see Table 3) will include standardized self-report questionnaires, task performance measures, and qualitative measures that will be collected at three timepoints (Months 0, 2, and 5). Additionally, at baseline, demographics will be collected for evaluation as potential confounds.

**Table 3 tab3:** Measurement description by domain.

	Type	Content	Category	Cronbach’s alpha	Items
EACQ	Explicit	Caregivers’ experiential avoidance	Relational well-being	0.60–0.71	15 items, 5-point Likert scale
ZBI-12	Explicit	Caregiver burden	Relational well-being	0.69–0.89	12 items, 5-point Likert scale
PAC	Explicit	Positive feelings from care provision	Relational well-being	0.80–0.86	9 items, 5-point Likert scale
IRI	Explicit	Empathic tendencies and feelings	Relational well-being	0.70–0.78	28 items, 5-point Likert scale
FCS	Explicit	Caregivers’ worry about compassion	Relational well-being	0.84–0.92	38 items, 5-point Likert scale
FCI-MS	Explicit	Perceived relationship quality	Relational well-being	>0.90	15 items, 5-point Likert scale
TASIT-SIE	Implicit	Assessing ability to detect sarcastic remarks and lies	Relational well-being	–	17 items, yes/no
HUMOR	Implicit	Assessing humor comprehension	Relational well-being	–	–
SDR	Implicit	Knowledge of social norms around emotional displays	Relational well-being	–	–
DASS-21	Explicit	Depression, anxiety, stress	Psychological well-being	0.86–0.90	21 items, 4-point Likert scale
DERS	Explicit	Trait-level emotion regulation ability	Psychological well-being	0.80–0.89	36 items, 5-point Likert scale
SPANE	Explicit	Positive & negative feelings associated to an experience	Psychological well-being	0.81–0.89	12 items, 5-point Likert scale
SES	Explicit	Perceived self-efficacy	Psychological well-being	–	4 items, 5-point Likert scale
FFMQ-SF	Explicit	Perceived levels of trait mindfulness	Psychological well-being	0.75–0.93	15 items, 5-point Likert scale
SCS-SF	Explicit	Caregivers’ self-compassion	Psychological well-being	>0.86	12 items, 5-point Likert scale
HEMA-R	Explicit	Psychological wellbeing	Psychological well-being	>0.80	10 items, 7-point Likert scale
WHOQOL-BREF	Explicit	Quality of life improvements	Psychological well-being	0.83	Domains, 5-point Likert scale
PES-AD	Explicit	Frequency of events & pleasantness of events	Dementia Patient Lifestyle	0.86–0.95	40 items, 3-point Likert scale

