As part of relational wellbeing, *emotion*, *connectedness*, and *rigidity* statements between caregivers and their care-recipients will be assessed *via* an audio-recorded 10-min semi-structured interview. Verbatim transcripts will be prepared and analyzed using a text analysis software Oedipus Text (Ascher et al., 2010; Connelly et al., 2020). We will assess socioemotional language usage in caregivers across three domains (see Supplementary material):

*Emotion*: Consistent with other studies of emotional language usage (positive and negative), a composite list consisting of words from the emotional lexicon state will be used.*Connectedness:* We will identify the number of pronouns in each of the following three lexical categories, as defined by the pronoun lexicon: we-words (pronouns referring to the couple), me-words (pronouns referring to the speaker) and you-words (pronouns referring to the other spouse).*Rigidity*: We will identify the number of rigid statements (e.g., never) regarding the care recipient’s behavior or characteristics, as defined by the rigidity lexicon.

After initial independent scoring, a consensus review will be performed to confirm reliability and validity of scoring for all analyses. For each domain, mean composites will be generated. In addition, exploratory qualitative analysis will be performed to examine themes in all three domains.

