## Discussion

This RCT protocol is designed to provide valuable information about the manner in which dementia caregivers’ well-being is improved by mindfulness-based interventions that are tailored to their specific lifestyle and stressors. Developing a capacity to broaden perspective without automatically reacting, a core mindfulness skill, may make the perceived relationship quality between caregiver and demented patient seem more mutual, connected, empathic and positive, despite the ongoing stressors of dementia care. Caregivers of persons with dementia receiving the 8-week mindfulness intervention may also gain a new perspective on their role as a caregiver, potentially resulting in increased positive affect and reframe their caregiving experience as more purposeful. Overall, this study will contribute to the evidence base concerning whether mindfulness-based interventions can be efficacious in empowering caregivers to regain relationship satisfaction and achieve greater equanimity in the face of their substantial stressors. In addition, this study will inform future studies with larger samples.

The design of the current protocol is subject to limitations. For instance, a small group size is necessary for the active intervention, leading to an overall small sample size, a selective recruitment pool, and an overall homogeneous sample. It is a risk that, if only a single caregiver group is run through the active intervention, the study might then be underpowered to definitively establish the effectiveness of the proposed intervention. However, additional rounds of intervention may increase the overall sample size to a more acceptable level of statistical power. While longer follow-up periods are very informative and important, the scope of our study is to measure short term effects of mindfulness-based interventions on caregiver wellbeing. Hence a 3 month follow up fit better our pilot study’s scope. Also, the study is designed to provide both qualitative responses and quantitative trends that will add to the existing evidence concerning the efficacy of mindfulness-based interventions for dementia caregivers. In addition, any social intervention it is contextualized to the dominant culture in which it was developed. Thus, this protocol may not generalize to other cultural and linguistic groups, and therefore a thoughtful and data-driven process should be used when adapting it more broadly to such groups.

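### The primary outcome is a domain of up to 12 measures, each tested at unadjusted 0.05, with no rule for which result decides the primary hypothesis

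*Protocol article*

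**What the plan says.** The Abstract sets the primary outcome at domain level: "The primary outcome will be relational well-being, and data will be analyzed using linear mixed modelling". The Introduction makes improvement in that domain, relative to active control, hypothesis A.

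The section on the primary outcome says "We included a number of measures of caregivers’ relational well-being" and ranks none of them. Table 3 lists nine under this heading: EACQ, ZBI-12, PAC, IRI, FCS, FCI-MS, TASIT-SIE, Humor and SDR. The same section adds the interview: "As part of relational wellbeing, *emotion*, *connectedness*, and *rigidity* statements between caregivers and their care-recipients will be assessed". On scoring these it says "For each domain, mean composites will be generated". That gives one composite per interview domain and none for relational well-being as a whole.

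The Data analysis plan fits a mixed model to every outcome measure. It names treatment group by time over t0, t1 and t2 as the main analysis, and also looks for treatment and time main effects. Its error rule is "All hypotheses will be individually evaluated at a nominal *p*-value of 0.05".

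The primary-outcome section words the hypothesis as a change from before to after the intervention, which points to T1. The analysis section does not carry this through. The Design section describes the study as an exploratory pilot.

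**The concern.** Hypothesis A has no stated criterion for success. Improvement on any one of 12 measures could be reported as support for the primary hypothesis, and nothing in the document says which measure was meant to count. The 5% error rate then applies to each test but not to the primary claim.

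This is not a detail left to a later analysis plan. The protocol makes the choice itself: the primary outcome is the domain, and each test stands alone at 0.05. At stake is whether a reported positive primary result could be told apart from the best of a dozen chance results, and whether later, larger trials would carry forward the right outcome.

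**Working it through.** **Inputs from the protocol article**
- Instruments in the primary domain: 9 (Table 3). Interview composites: 3 (primary-outcome section). Total 12.
- Level per test: 0.05 (Data analysis plan). Sidedness is not stated; two-sided is assumed.
- Main test per measure: group by time (Data analysis plan).
- Sample size: 20 per arm with 80% expected retention, so 0.80 × 20 = 16 per arm.

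**Assumptions.** There is no true effect on any measure. The correlation between measures is not given, so 0, 0.3 and 0.5 are shown.

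**Step 1: the plan's own figure.** It states 0.05 per hypothesis and no domain-level error rate. A null simulation (2 groups, 3 times, random intercept, 16 per arm, assumed intraclass correlation 0.6, 20,000 runs) gave 0.049 to 0.052 for a single group-by-time test. The nominal level therefore holds for one test.

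**Step 2: at least one p<0.05, either direction, one test per measure.** With k independent tests the chance is 1 − 0.95^k.
- k = 9: 1 − 0.95^9 = 0.370
- k = 12: 1 − 0.95^12 = 0.460

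Equicorrelated normal statistics give:

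| Measures | ρ = 0 | ρ = 0.3 | ρ = 0.5 |
|---|---|---|---|
| 9 | 37% | 33% | 27% |
| 12 | 46% | 40% | 32% |

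The mixed-design simulation agrees within about one percentage point (9 measures: 37%, 33%, 28%; 12 measures: 46%, 40%, 33%).

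**Step 3: only results favouring mindfulness.** Hypothesis A is directional, so the favourable tail is the relevant one: 1 − 0.975^k.
- k = 9: 1 − 0.975^9 = 0.204
- k = 12: 1 − 0.975^12 = 0.262, falling to about 20% at ρ = 0.3 and 16% at ρ = 0.5

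This treats each test as a single-degree-of-freedom contrast. The three-time-point interaction has two degrees of freedom and no direction of its own. For one pre-specified test the matching figure is 2.5%.

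**Step 4: wider counts, as a range only.**
- Treatment main effect plus interaction on 12 measures (24 tests), simulated, either direction: 71%, 64% and 55% at ρ = 0, 0.3 and 0.5.
- Subscale scores: the count depends on how TASIT-SIE and the interview are split, which the article does not settle. With two TASIT-SIE scores and three interview composites it is 24. With four and six it is 29. One test each, either direction, gives 1 − 0.95^24 = 0.708 and 1 − 0.95^29 = 0.774 if independent. At ρ = 0.5 these are about 46% and 50%.

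**Step 5: after a correction.** One measure and one contrast return the error to 5%. Keeping 12 co-primary measures under Bonferroni needs 0.05/12 = 0.0042 per test. For an unadjusted two-sample comparison at 16 per arm, the standardised difference detectable with 80% power would then rise from 1.02 to about 1.41. With nine measures (0.05/9 = 0.0056) it would be about 1.37.

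**The case against.** The strongest reply is that this is a declared pilot. The article says it is powered only for large effects, undertakes to report preliminary effect sizes for all measures, and openly calls its 0.05 nominal. On that view familywise control is a matter of preference. This lowers the severity. It does not answer the point, because the plan still names a primary outcome, states a directional hypothesis for it and sets a threshold, without saying which test the threshold applies to.

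The other side also rightly limits the claim in these ways:
- **Contrast and time are partly fixed.** Group by time is the stated main analysis, and the hypothesis wording points to T1. A time main effect cannot support a between-group hypothesis, so counting three tests per measure overstates the routes to a positive result.
- **Testing the interview composites at 0.05 is an inference.** It follows from the statement that all outcome measures are modelled, but the analysis section describes only thematic analysis for the interviews. Without them, the nine-instrument figures apply.
- **Subscale counts are not firm.** Only PAC's three scores are expressly described as usable on their own in analyses.

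A reader might also infer that the Discussion plans to add participants until significance is reached, since it says "additional rounds of intervention may increase the overall sample size to a more acceptable level of statistical power". The text does not support that. It is a remark about limitations, with no interim look, trigger or pooled retest, and the recruitment section fixes enrolment at 40. Nor does it follow that published effect sizes will be inflated by selection on p<0.05, given the undertaking to report all of them.

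**Conclusion.** The point holds at moderate severity. The primary hypothesis rests on nine to 12 measures, with no lead measure, composite or decision rule, at an unadjusted 0.05 each. With one test per measure and no true effect, the chance of at least one significant result is 37% (nine) to 46% (12) under independence, and about 27% to 32% at correlation 0.5. In the favourable direction, 12 measures give 26% down to 16% over the same correlation range, against 2.5% for a single test. These figures assume two-sided tests, equal pairwise correlation and no effect on any measure.

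A reader might go further and say that a positive primary result is likely by chance alone, or that the trial could almost always find support. The figures do not show that. With one test per measure every value is below one half. The either-direction chance passes one half only if the treatment main effect is also counted, or in most cases if subscales are, and the document does not say that either would decide hypothesis A.

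**What to change.** Before any results are seen, amend the protocol and registry wording as follows.

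1. Name one primary measure and one primary contrast: the mindfulness-versus-control difference in change from T0 to T1, taken from the planned group-by-time model. This matches the wording of the hypothesis. FCI-MS is a defensible choice: Table 3 describes its content as "Perceived relationship quality" and gives an alpha above 0.90. It does not cover the reading of social signals, which the hypothesis also includes. If both aspects are to count, a composite of the domain with components, weights and direction fixed in advance is an acceptable alternative.
2. Make the remaining relational measures secondary. Report each with an effect size and 95% confidence interval. Either label them exploratory or make claims only after Holm or false-discovery-rate adjustment within the domain.
3. State that the planned enrolment of 40 is the cohort for this analysis, and that any later round will be analysed as a separate cohort.

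The cost is wording only: no new data, visits or participants. The sponsor commits to one measure or composite and gives up unadjusted claims on the others.
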